#### Step 4 - design of the intervention

Based on the process of Intervention Mapping, the primary aims of the intervention are:

1) Improving older workers' mental factors of vitality by relaxation exercises;

2) Improving older workers' physical factors of vitality by vigorous intensity physical activity.

Additionally, the secondary aim of the intervention is to improve older workers' dietary habits by increasing intakes of fruit. The intervention will last 6 months and will consists of 1) three visits to a Personal Vitality Coach (PVC) combined with 2) the Vitality Exercise Programme (VEP), and 3) provided free fruit at the VEP.

##### Personal Vitality Coach (PVC) Visits

All participants will be invited to visit the PVC three times during 6 months. The first visit (30 minutes) will be at the start of the intervention, the follow-up visits (30 minutes) will be at 4-6 weeks and 10-12 weeks after the first PVC visit.

The coaching visits will be aimed at: 1) goal setting, 2) feedback on formulated goals (i.e. self-monitoring, self-evaluation), and 3) problem solving.

##### The Vitality Exercise Programme (VEP)

The VEP will be aimed at improving both mental and physical factors of vitality. Mental factors will be improved by yoga (relaxation exercises) and physical factors by a workout aimed at improving aerobic fitness and muscle strength. The VEP consist of:

1) a guided group session of yoga once a week,

2) a guided workout group session consisting of aerobic and resistance exercises once a week

3) aerobic exercising without direct face-to-face instruction. Attendance to this once a week additional session will be prescribed by the fitness instructor who guides the workout sessions, and by the PVC during the visits.

##### Yoga

Yoga will be guided by a qualified yoga instructor and will be provided once a week (in total 24 sessions during a intervention period of 6 months) in small group sessions (max. 16 persons) and consists of relaxation exercises. Each session will last 45 minutes and will start with relaxation and preparation postures for the hips, shoulders, neck, feed, and hands while focussing on breathing (5 minutes), followed by a series of standing postures, forward bending postures and twists, and light back bending postures (30 minutes). Each yoga session will be ended with an yoga exercise aimed at total relaxation, known as the 'Savasana Corpse Pose' and mediation (10 minutes).

##### Workout

The workout will be guided by a fitness instructor and will be provided once a week (in total 24 sessions during a intervention period of 6 months), and will be conducted in small group training sessions (max. 16 persons). Each session will last 45 minutes, and will start with a warming-up of 5 minutes followed by aerobic exercises (in total 2 × 10 minutes, 1 × 5 minutes = 25 minutes), resistance training (2 × 5 = 10 minutes), and a cooling-down (3 minutes).

Improvements in aerobic fitness (i.e. VO_2_-max) are directly related to the frequency, intensity, and duration of the activities. The intensity of the workout will meet the ACSM-guidelines, which recommends an intensity that equals 65-90% of the maximum heart rate (HR_max_) [47,49]. The resistance training will be progressive in nature and provides stimulus to all major muscle groups. The ACSM-guidelines recommend a repetition maximum (RM) of 10-15 repetitions of each exercise. The frequency of the resistance exercises was defined as 3 RM (3 × 10-15 repetitions). Each exercise will be performed with a load at which the repetition maximum can just be maintained [48].

##### Aerobic exercise without direct face-to-face instruction

Besides the yoga and workout sessions, older workers will be prescribed to perform once a week for at least 45 minutes of vigorous physical activity without face-to-face instructions (e.g. fitness, running, spinning). To achieve improvement in aerobic fitness, workers will be asked to exercise with an intensity similar to the guided workout sessions. As an illustration of this intensity, workers got the instruction to exercise with an intensity at which they become sweating and experienced increased respiration and heart beat.

##### Providing free fruit at the VEP

During the intervention period, free fruit will be provided at the guided yoga and workout group sessions of the VEP.

#### Step 5 - Adoption and implementation plan

Two main factors for adoption of the programme by the target population were identified, namely time and place. Therefore, the lifestyle programme was modified to fit within a common working day of the older workers by choosing adequate time schedules for the provided yoga and guided workout group sessions. Guided group sessions will be provided in two time blocks on all working days: 1) during lunchtime (3 sessions), and 2) after working hours (3 sessions). Furthermore, to increase the adoption of the lifestyle programme, the guided group sessions will be provided near the worksite (max. 5-10 minutes walk).

#### Step 6 - Evaluation plan

The (cost-) effectiveness of the lifestyle intervention developed in the preceding IM steps, will be evaluated in a randomised controlled trial (RCT) with two arms. During six months, employees in the intervention group will receive the lifestyle programme as described above. The control group will receive the same written information as the intervention group about a healthy lifestyle (physical activity, relaxation, fruit). Both groups will be measured at baseline, and after 6 and 12 months. The Medical Ethical Committee of both the VU University Medical Center (VUmc, Amsterdam, the Netherlands) and the Leiden University Medical Center (LUMC, Leiden, the Netherlands) approved the study protocol.

##### Study population

The study population consists of older workers (aged 45 years and over) from the VUmc and LUMC, working at least 16 hours a week.

##### Recruitment of the study population

First, all potential participants will receive an invitation letter at their home postal address together with an information package consisting of: 1) flyer with information about the study, 2) informed consent, 3) screener for exclusion criteria: i.e. the physical activity readiness questionnaire (PAR-Q), and 4) a stamped and addressed envelope for reply. Workers who are willing to participate in the study will be asked to return the signed informed consent together with the completed screener within a week. Subsequently, workers who meet the inclusion criteria and signed the informed consent will receive the baseline questionnaire together with an invitation for the UKK walk test at their home postal address. Workers who are not willing to participate in the study will be asked to give their reasons for not participating. Two weeks after the initial mailing, a postcard will be sent to thank respondents for returning their screener and informed consent. For non-respondents the back of this postcard will be used as a reminder and as a second opportunity to complete the screener and informed consent. To minimise non-response during the follow-up measurements, all participants will receive a pre-notice card a week before the measurement. Subsequently (i.e. within one week after the pre-notice card), all participants will receive the follow-up questionnaire and will receive an invitation for another UKK walk test.

##### Randomisation procedure

A computer-generated randomisation will be performed at individual level after baseline measurements are completed. Randomisation will be executed, after completing baseline measurements, by an independent researcher (i.e. research assistant) using Random Allocation Software (Version 1.0, May 2004, Isfahan University of Medical Sciences, Iran).

##### Power calculation

The sample size calculation will be based on differences between the intervention and control group with regard to changes in the mean vitality score, measured by the Utrecht Engagement Scale (UWES) (10). Based on a study among 10.000 Dutch and Belgian employees, the baseline mean vitality score (range 0-6) is assumed to be 3.99 (SD = 1.11) [12]. For the sample size needed, a difference in the vitality mean score of 10% between the intervention and control group after six months will be considered relevant. This means an average difference in the vitality mean score of 0.4 (SD 1.2) between both study groups. Assuming α = 0.05, power = 0.90, and two-sided tests, 189 participants per group will be needed. Taking into account a loss of follow-up of 15%, a sample size of 446 employees (223 employees in each group) needs to be included. Further, based on an initial response of 20% of the eligible workers (i.e. workers aged 45 and over), 2230 workers need to be approached and asked to participate in the study. In total, 3756 older workers of the two academic hospitals will be approached for participation, thereby ensuring sufficient statistical power, even in case of unexpectedly poor initial response and/or high loss to follow-up.

## Measurements

All measurements will be completed at baseline, after 6, and 12 months. The measurements will consist of 1) a questionnaire, containing questions concerning lifestyle, vitality, general health, work and the health-related fitness construct Body Mass Index (BMI) and waist circumference, combined with 2) the 2-km UKK walking test.

### Lifestyle

The level of physical activity will be assessed using the validated Short Questionnaire to AssesS Health enhancing physical activity (SQUASH) [50]. The SQUASH measures duration, frequency and intensity of four clusters of physical activity, i.e. commuting activities, household activities, activity at work, and leisure time activities. The SQUASH has been shown to be a fairly reliable and reasonably valid questionnaire [50].

In addition, physical activity will be measured objectively in a random sample of 200 participants of both the intervention (n = 100) and control group (n = 100). This subsample will receive during a period of one week (7 days) an accelerometer (GTM1 ActiGraph, ActiTrainer ActiGraph), which registers the actual physical activity during daytime. To minimize both the intrainstrument variability (the difference within a single accelerometer over multiple follow-up measurements) and interinstrument variability (differences between different accelerometers during a single measurement), workers receive every follow-up measurement the same accelerometers. The accelerometers will be worn during waking hours on the right hip and will be handed out after completing the questionnaire. Fruit intake will be assessed using an adapted version of the validated Short Fruit and Vegetable questionnaire [51]. The questionnaire consists of 10 questions: 6 about fruit consumption and 4 about consumption of vegetables. In this study, only the questions about fruit will be asked.

### Vitality

A 17-item questionnaire, called the Utrecht Engagement Scale (UWES), will be used to measure workers' work engagement. The UWES consists of three aspects: vitality (6 items), dedication (5 items), and absorption (6 items) [11,12,52].

Vitality will be assessed by the six items of the UWES that refer to high levels of energy and resilience, the willingness to invest effort, not being easily fatigued, and persistence in the face of difficulties.

### Health-related fitness

BMI will be calculated using self-reported weight and height. All participants will be asked to report their self-measured waist circumference in each questionnaire. For that aim, a measuring tape (range 0-135 cm) will be sent to all participants along with the questionnaires. Participants will have instructions on how to use the measuring tape and are asked to report their waist circumference to the nearest cm. Besides BMI and waist circumference, the aerobic fitness (VO_2_-max) of the older workers will be measured using the UKK 2-km walking test. The optimal way of measuring VO_2_-max is by a maximal exercise test (i.e. treadmill test). However, for regular use in many research and clinical setting, this may be impractical. For simplicity, suitability and social acceptability walking is an attractive exercise mode for the purposes of mass testing [53]. Therefore, in this study the UKK walk test will be used to predict VO_2_-max. The UKK walk test is a simple and safe test designed to measure the aerobic fitness of normally active men and women [54]. The UKK walk test is a fast 2-km walk supplemented with simple measurements (heart rate, BMI) and has shown to be a feasible and accurate method for predicting VO_2_-max in healthy 20-65 year old subjects [55]. A gender-specific prediction model including walking time, heart rate at the end of the walk, age and body mass index predicted 73-75% of the variance in VO_2_-max [53].

### General health

Information about whether or not suffering from any chronic diseases (e.g. cardiovascular diseases, respiratory diseases, muscoskeletal disorders, diabetes mellitus) will be obtained using a 1-item question about chronic diseases from the Dutch Working Conditions Survey [56]. Mental health will be measured using the 5-item scale of the RAND-36. Besides mental health, other health-related quality of life items will be measured: physical functioning (PH, 10 items), role limitations caused by physical problems (RP, 4 items), general health perceptions (GH, 5 items), and vitality (VT, 4 items) [57].

### Work-related outcomes

Sick leave will be determined using the World Health Organization Health and Work Performance Questionnaire (WHO-HPQ) measuring loss of productivity due to decreased performance while at work (presenteeism) and sick leave (absenteeism). This questionnaire has shown good concordance with employer records of work absenteeism and critical incidents [58,59]. For the specific purpose of the economic evaluation, participants will be asked to complete the WHO-HPQ once every three months. Besides loss of productivity, the need for recovery after a working day will be measured using the 11-item 'need for recovery scale' from the Dutch version of the Questionnaire on the Experience and Evaluation of Work (Dutch abbreviation VBBA) [60].

### Data analysis

#### Statistical analysis

The effectiveness of the lifestyle intervention will be analysed by means of a regression analysis (analysis of covariance) with the outcome measure at follow-up (6 months and 12 months) as the dependent variable and adjusting for the baseline levels of the outcome measure. Both crude and adjusted analyses will be performed. In the adjusted model, other potential confounders than covariates will be included, such as age, smoking and physical activity. Furthermore, effect modification, e.g. by gender, will be checked. All statistical analyses will be performed according to the intention-to-treat principle. For all analyses a two-tailed significance level of < 0.05 will be considered statistically significant. Linear and logistic (longitudinal) regression analyses will be performed with SPSS 15.0 (SPSS Inc. Chicago, Illinois, USA).

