**Methods:**

Using the Intervention Mapping (IM) protocol, a lifestyle intervention was developed based on information obtained from 1) literature, 2) a short lifestyle questionnaire aimed at indentifying the lifestyle behaviours among the target group, and 3) focusgroup (FG) interviews among 36 older workers (aged 45^+ ^years) aimed at identifying: a) key determinants of lifestyle behaviour, b) a definition of vitality, and c) ideas about how vitality can be improved by lifestyle.

The main lifestyle problems identified were: insufficient levels of physical activity and insufficient intake of fruit and vegetables. Using information from both literature and FG interviews, vitality consists of a mental and a physical component. The interviewees suggested to improve the mental component of vitality by means of relaxation exercises (e.g. yoga); physical vitality could be improved by aerobic endurance exercise and strength training.

The lifestyle intervention (6 months) consists of three visits to a Personal Vitality Coach (PVC) combined with a Vitality Exercise Programme (VEP). The VEP consists of: 1) once a week a guided yoga group session aimed at relaxation exercises, 2) once a week a guided aerobic workout group session aimed at improving aerobic fitness and increasing muscle strength, and 3) older workers will be asked to perform once a week for at least 45 minutes vigorous physical activity without face-to-face instructions (e.g. fitness). Moreover, free fruit will be offered at the group sessions of the VEP. The lifestyle intervention will be evaluated in a RCT among older workers of two major academic hospitals in the Netherlands. At baseline, after 6 and 12 months, measurements (primary: lifestyle and vitality, and secondary: work-engagement and productivity) will take place.

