#### Economic evaluation

A cost-effectiveness analysis (CEA) will be performed from the company perspective. The time horizon will be 12 months, similar to the trial. The analysis will be performed according to the intention-to-treat principle. Missing data will be imputed using multiple imputation techniques. The primary outcome measurements in the CEA will be lifestyle (physical activity and daily fruit intake) and vitality (total score vitality scale UWES).

Two CEAs will be performed from the company perspective:

1) intervention costs together with savings as a result of reduced sick leave (absenteeism) and loss of productivity (presenteeism) will be compared to the obtained effects on the primary outcome measures lifestyle and vitality

2) intervention costs will be compared to the obtained benefits due to reduced sick leave and increased productivity.

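### The stated 5% error and 90% power fit one test, UWES vitality at six months, yet several outcomes are primary and every analysis is tested at an unadjusted 0.05

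*Protocol article*

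**What the plan says.** Five places in the protocol article bear on this.

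- **Abstract, Methods** ranks the measurements as "primary: lifestyle and vitality, and secondary: work-engagement and productivity". Lifestyle is not broken down there.
- **Economic evaluation** breaks it down, for the cost-effectiveness analysis (CEA): "The primary outcome measurements in the CEA will be lifestyle (physical activity and daily fruit intake) and vitality (total score vitality scale UWES".
- **Step 4, design of the intervention** gives fruit a lower rank: "the secondary aim of the intervention is to improve older workers' dietary habits by increasing intakes of fruit".
- **Power calculation** uses one outcome at one time: "a difference in the vitality mean score of 10% between the intervention and control group after six months will be considered relevant". It states 0.4 (SD 1.2), two-sided α of 0.05, power 0.90, 189 per group, and 223 per group after 15% loss.
- **Statistical analysis** specifies analysis of covariance "with the outcome measure at follow-up (6 months and 12 months) as the dependent variable", adds "Both crude and adjusted analyses will be performed", plans checks of effect modification, and fixes the threshold: "For all analyses a two-tailed significance level of < 0.05 will be considered statistically significant". It singles out no outcome, time or model as the deciding one.

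**The concern.** The sample size supports one comparison at the stated error rate and power. The outcomes labelled primary form a larger set, each can be analysed at two follow-ups, and the same 0.05 applies to each result without adjustment. Nothing in the text prevents a single significant result, for example fruit intake at 12 months, from being reported as showing that the programme works. The Conclusion makes the benefit to companies and society depend on proven effectiveness, so it matters which result carries that claim and at what error rate.

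Fruit intake adds a plain inconsistency. It is among the primary measures in the Economic evaluation and a secondary aim in Step 4. The number of primary comparisons depends on which of these governs.

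**Working it through.** **1. The plan's own sample size.** Inputs from the Power calculation: difference 0.4, SD 1.2, two-sided α 0.05, power 0.90.

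n per group = 2 × (1.9600 + 1.2816)² × 1.2² / 0.4² = 2 × 10.508 × 9 = 189.1. The article has 189; rounding up gives 190, which is immaterial. Power with 189: √(189/2) × 0.4/1.2 = 3.240; 3.240 − 1.960 = 1.280; Φ(1.280) = 0.900. After 15% loss: 189 / 0.85 = 222.4, so 223 per group and 446 in total, as stated. The sizing is sound for one outcome at one time.

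**2. Counting the primary comparisons.** The article allows several readings: vitality at six months only (1 test); vitality at both times (2); vitality and physical activity at both times, with fruit secondary as in Step 4 (4); vitality, physical activity and fruit at both times, as the Economic evaluation lists them (6). Crude and adjusted versions and the effect-modification checks are not counted.

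**3. Chance of at least one false positive.** This supposes that there is no true effect and that any one result below 0.05 is taken as success. For k independent tests it is 1 − 0.95^k. Correlated normal test statistics were also simulated (800,000 draws per scenario), with between-time correlation 0 to 0.8 and between-outcome correlation 0 to 0.5. The article gives no correlations, so these are assumptions.

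| Reading | Tests | Independent | Over the assumed correlations |
|---|---|---|---|
| Vitality, 6 months | 1 | 5% | 5% |
| Vitality, both times | 2 | 9.75% | 7.8–9.7% |
| Two outcomes, both times | 4 | 18.5% | 13.9–18.6% |
| Three outcomes, both times | 6 | 26.5% | 18.9–26.6% |

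The top of each simulated range is the zero-correlation case and differs from the exact value only by simulation error. For three outcomes with between-time correlation 0.5–0.7 and between-outcome correlation 0–0.3, the simulated range is 21.9–24.8%.

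**4. If a longitudinal model gave one overall test per outcome.** Under independence: two outcomes 1 − 0.95² = 9.75%; three outcomes 1 − 0.95³ = 14.3%.

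**5. What six equal primary tests would cost.** Bonferroni: 0.05/6 = 0.0083, critical value 2.638. Power for vitality with 189 per group: Φ(3.240 − 2.638) = Φ(0.602) = 0.73. For 90% power: 2 × (2.638 + 1.2816)² × 9 = 276.5, so 277 per group, and 277 / 0.85 = 325.9, so 326 after loss. This covers vitality only; no effect size is given for physical activity or fruit.

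**The case against.** **Rival primary sets.** A reader might infer that the article declares conflicting sets of primary outcomes. It does not. The Abstract and the Economic evaluation are the two places that use the label for outcomes, and they agree; the second spells out the first, for the CEA. Step 4 lists aims of the intervention, and sizing a trial on one of several outcomes is ordinary practice. What remains is fruit, whose rank differs between Step 4 and the Economic evaluation.

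**A flat error rate of about a quarter.** A reader might infer this too. It requires three primaries, a separate test at each follow-up, low to moderate correlation, and a rule that any one success suffices. The article states neither the correlations nor such a rule. If Step 4 governs fruit, there are four tests rather than six. The upper end also treats 6- and 12-month scores from the same people as unrelated, which is implausible.

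**Longitudinal models.** The Statistical analysis section also mentions longitudinal regression, which could yield one overall effect per outcome. That would reduce the count. With more than one primary outcome it would not by itself return the error to 5%.

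**A condensed article.** A testing hierarchy may sit in a full protocol or SAP that is not shown, and its absence here is not the point. The point is what the article does fix: more than one primary outcome, one unadjusted threshold for every analysis, and a sample size for a single comparison. The Power calculation suggests that vitality at six months is the main comparison, but does not say that it decides the trial.

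**Crude, adjusted and interaction analyses.** Two versions of one comparison are highly correlated, and interaction checks are not claims of overall effect. Choosing between the two versions after seeing them could add to the error, but that is not quantified here.

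**Conclusion.** The concern holds in a limited form. The sample size is right for its own inputs. The stated error rate and power, however, belong to one of several comparisons that the article treats as primary, and the text applies 0.05 to all of them without saying which one decides. Depending on the reading, the chance of at least one false positive runs from 5% (vitality at six months alone) through 8–10% and 14–19% to 19–27%. Every figure above 5% depends on an any-one-suffices rule that the article does not state and on assumed correlations, so the range should be quoted with those conditions and no single value presented as the trial's error rate. The difference in fruit's rank needs no assumption and must be reconciled in any case.

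**What to change.** In Statistical analysis, name UWES vitality at 6 months, from one specified baseline-adjusted model at two-sided 0.05, as the single primary test. This gives 5% error and about 90% power with the planned 189 per group.

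Test physical activity and fruit intake at 6 months as key secondary outcomes with a procedure fixed in advance, such as Holm or a fixed sequence, and say whether that testing depends on the primary result. Report the 12-month results, the other of the crude and adjusted models, and the effect-modification checks as supportive estimates with confidence intervals.

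Bring the Abstract and Step 4 into line with this order. The Economic evaluation may keep physical activity, fruit and vitality as its effect measures, but should not call them the trial's primary outcomes.

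The cost is that physical activity and fruit lose stand-alone primary status, a real change to what the Abstract declares. No extra participants are needed. By contrast, keeping all six comparisons primary under Bonferroni would leave about 73% power for vitality, or need 326 per group (652 in total) instead of 223 (446).
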